### Intervention and comparator

2.5

#### Navigator intervention

2.5.1

All participants (regardless of treatment group) will receive usual healthcare as per their treating medical team (see section B.5.2).

The Navigator intervention was designed with input from multiple stakeholder groups, including patients, their caregivers, front-line hospital-based and ambulatory clinicians (hospitalists, primary care, cardiology, hematology, pulmonary, social work), and hospital administration (quality improvement and population health leadership) [18]. Stakeholder engagement was used to ensure the Navigator intervention directly addressed end-user requirements and would be feasible to implement. The intervention will be delivered by CHWs and peer coaches during the index hospitalization and continued for two months after hospital discharge. The two CHWs for the PArTNER study (both women; one Latino who was bilingual, Spanish and English; the second was black and spoke English) were carefully selected to have at least a General Educational Development (GED) or high-school diploma, a passion for working in the communities served by UI Health (primarily west and southside Chicago), and a valid driver's license. The CHWs received education from investigators and staff on the health conditions of interest, techniques for approaching and connecting with patients in the hospital setting, safety during home visits, and appropriate documentation of interactions with study participants. The project manager for the study was responsible for daily supervision, with the help of a nurse practitioner and physicians on the study team.

The peer coaches are staff at existing patient advocacy organizations (Section B.5.1.2). Peer coaches are required to have a telephone and internet access at home to facilitate training, data entry, and rapidly retrieving information about the communities in which patient lived. Peer coaches underwent training that included a 45-h web training session on 1) customer service and call etiquette, 2) the Health Insurance Portability and Accountability Act (HIPAA), 3) basic training about the health conditions that formed the target population, 4) program-specific training for PArTNER and how to find community resources (e.g., food pantry, transportation, housing), and 5) use of a HIPAA-compliant portal to document all calls. The curriculum was based on training that was used by the COPD Foundation for its call-center and supplemented with information relevant to the PArTNER study. The number of peer coaches varied during the course of the PArTNER study but at least ten peer coaches were involved in the study at any particular point. The CHW and peer coaches were instructed to use a HIPAA-compliant web-based database to record interventions completed for each study participant.

##### CHW-led interventions (Table 2)

2.5.1.1

The CHWs interviewed participants in person during the index hospitalization and at a home visit within three days of hospital discharge. The goal of these CHW-led sessions was to identify barriers to health and healthcare and to provide support to promote self-management skills. Potential resources for participants will be accessed using an interactive online resources database that allowed identification of hyper-local resources to each unique participant [28]. The CHW intervention is flexible to allow it to occur via phone or around the time of follow-up appointments at UI Health if needed. The initial visit is scheduled to occur over approximately 45 min. The number of visits conducted by the CHW during hospitalization is dependent on participants’ needs and length of stay; participants will receive daily visits in some cases.

##### Peer-coach-led interventions (Table 3)

2.5.1.2

The telephone-based peer coaching support at weeks 1 (intervention window 6–10 days), 2 (12–16 days), 3 (19–23 days), 5 (32–37 days), and 7 (47–51 days) after hospital discharge is intended to continue supports initiated by the CHW intervention (Fig. 1). Each peer coach call is scheduled for approximately 15 min, while each participant could have had more than one peer coach across the five calls (mimicking real-world circumstances). Patient advocacy organizations will provide peer coaching support for participants hospitalized with pneumonia or COPD (COPD Foundation), myocardial infarction or heart failure (Mended Hearts), and sickle cell disease (Sickle Cell Disease Association of Illinois) [[29], [30], [31]]. The “peer coaching” intervention by phone is intended to leverage existing services and to connect participants with resources in the community. The COPD Foundation has a well-developed peer coaching (patients with COPD or caregivers of patients with COPD) infrastructure that provides a method for tracking and recording peer coaching phone calls. If a peer coach is not available from the specified organization, the CHW would temporarily fill-in to complete peer coaching calls. Through the HIPAA-secure database, peer coaches have access to the CHW-completed *Barrier Assessments* and *Discharge Patient Educational Tool (DPET*; see online supplement) that is specific to their patients, helping to facilitate a team response and to know each participant's unique needs. Over the course of approximately 60 days post-discharge, peer coaches will use a sequence of up to five phone calls to provide support in addressing barriers to care and the use of the DPET to promote self-management. Up to four call attempts will be made for each peer coaching call (will attempt to leave voicemails after each unsuccessful call attempt).

#### Usual care

2.5.2

Because usual hospital-to-home transitional care can vary within and across institutions, we plan to review the discharge documentation in the electronic health record for all participants (regardless of treatment group) to evaluate care provided by the clinical teams. This review will be conducted by study staff who are masked to treatment allocation sequence. We used stakeholder input and the framework proposed by the Society of Hospital Medicine's BOOST Program (“universal discharge checklist”) to define the eight transitional care elements of interest in describing usual care (yes or no; Table 4) [12]. Front-line clinicians who provide care to patients with target conditions for the PArTNER study agreed with the definitions for each of eight transitional care indicators in Table 4. In a random 10% sample of study participants, a second research coordinator will repeat the data abstraction to assess inter-rater agreement (kappa statistic). All discrepancies will be reviewed, adjudicated, and corrected values will be entered into the study database.

**Table 4 tbl4:** Description of Universal Discharge Components used in the PArTNER study to evaluate care provided by the participant's clinical team.

Universal Discharge Component	Description
A. Medication reconciliation performed on the date of discharge	Medication reconciliation marked as complete and/or a pharmacist note documenting medication reconciliation in the electronic health record.
B. Medication education provided to patient on date of discharge	Educational materials specific to a class of medications, a specific medication, or device (e.g., respiratory inhaler, oxygen equipment) provided to patient and/or pharmacist note documenting the education in the electronic health record.
C. Education on diagnosis, prognosis, self-care requirements, or procedures provided to patient on the date of discharge	Educational materials for any medical conditions listed in the discharge summary is documented in the electronic health record's Patient Education Note.
D. Disease management education provided to patient on the date of discharge	Instructions about how to seek additional care in case of clinical deterioration, or specific to the patient's medical condition recorded in the electronic health record.
E. Structured Discharge Summary completed upon hospital discharge:	Discharge summary recorded as finalized by the attending physician in the electronic health record within two [2] business days of hospital discharge.
F. Phone contact attempted within two business days post discharge with patient or caregiver.	Call attempt documented in the electronic health record as successful or unsuccessful within two [2] business days after hospital discharge.
G. Follow-up appointment within seven days of hospital discharge is specified in discharge instructions	Appointment information (at a minimum: location, date, time) in the electronic health record with at least one provider scheduled for seven or fewer days after hospital discharge; the provider location could be outside of the index hospital-affiliated clinics.
H. Discharge instructions provided to patient on the date of discharge	Documentation in the electronic health record that discharge instructions were provided to patient on the same date as discharge.

Footer: Study staff masked to treatment group assignment reviewed the electronic health record for all study participants to assess the presence or absence of each discharge component (see Methods for details).

### Study setting

2.6

The PArTNER study is a single-center clinical trial that enrolls patients hospitalized at UI Health. UI Health hospital is the largest state-supported hospital in Illinois and includes a 495-bed tertiary care hospital, 22 outpatient clinics (primary care and specialty care), and 11 federally qualified health centers. UI Health is a MSI (hospitalized patients are ∼80% Black) and represents an ideal environment to evaluate the effectiveness of care transition services tailored to this high-risk population.

### Time frame for the study

2.7

The intervention will span over a two-month period after hospital discharge (Fig. 1). Outcomes will be assessed at 30 days and 60 days. This outcome assessment time frame was selected not only to inform patients, caregivers, and other decision-makers about the potential of the Navigator interventions to address short-term measures of health on completion of the intervention (60 days), but also to provide information on the effect of the intervention on outcomes of interest to payers and health systems administrators, such as 30-day readmissions and deaths. There was insufficient stakeholder support for a longer (and more resource intensive) intervention and follow-up period.

### Data collection and sources

2.8

The ascertainment of outcomes after hospital discharge will be performed by a trained research coordinator who is masked to treatment group allocation. The research coordinator will attempt to contact participants by telephone. Up to 14 call attempts will be made to collect patient-reported outcomes for each of the 30- and 60-day assessments. Electronic health records will also be reviewed to assess outcomes, particularly healthcare utilization, at 30- and 60-days post-discharge.

Many aspects of our study design are intended to reduce the frequency of missing data. We designed the study to target a population not adequately served by current services, which could help serve as an incentive for clinicians to support the study and for participants to remain in the study. We will accommodate individual preferences as much as possible when setting follow-up visits or data collection time-points. The study enrollment and data collection will be performed as participants receive routine care in the hospital and with reduced burden post-discharge (e.g., data collection by phone, rather than in-person). Also, we do not equate treatment discontinuation with study drop-out; we will encourage participants to continue in the study and provide outcomes data even if they no longer wish to remain in the treatment group assigned by randomization. We will also encourage participants to continue in the study by explaining the importance of completing the study with as many participants as were enrolled to avoid selection bias. Reasons for withdrawing from the study or lost to follow-up will be collected when possible by interviewing study participants, caregivers, and review of electronic health records (e.g., participant died), and reporting the information in a participant flow diagram.

### Data and safety monitoring

2.9

Study procedures and updates will be reviewed during meetings with an independent Data and Safety Monitoring Board (DSMB) with 5 members: 3 physicians (2 hospitalists, 1 geriatrician), 1 pharmacist, and 1 nurse who provide direct patient care. The DSMB will be asked to review and approve the study protocol prior to initiation of participant recruitment and to convene twice yearly to review the study progress and make recommendations, including continuing study without modifications, continuing study with modifications, and terminating the study. We will submit draft written agendas prior to meetings and written summaries of discussions and next steps after each meeting.

### Study outcomes

2.10

#### Primary outcomes

2.10.1

Patient and caregiver engagement activities indicated the need for two co-primary outcomes for the clinical trial:1.Change in participant anxiety from baseline (enrollment to 30 days post-discharge).2.Change in participant informational support (enrollment to 30 days post-discharge).

Informational support refers to the ability to obtain advice, guidance, suggestions, or useful information.

We will use the National Institutes of Health (NIH) PROMIS measures for our co-primary outcomes, since the development and validation of PROMIS scales have been extensively documented [27]. The PROMIS emotional distress-anxiety short form (version 1.0 SF4a, 4 items) will be used to assess participant anxiety in the previous 7 days. The PROMIS informational support short form (version 2.0 SF4a, 4 items) will be used to assess informational support among study participants in the previous 7 days. For PROMIS measures, raw scores for each measure will be re-scaled into a standardized T-score with a mean of 50 and standard deviation of 10 for the US general population [27,32,33]. Higher PROMIS T-scores indicate more of the concept being measured (e.g., higher anxiety T-scores indicate more anxiety). Studies suggest that a 2- to 5-unit or greater difference in T-scores is likely to be the MCID, though the MCID following hospital discharge in the target population has not been established.

Using PROMIS measures confers several distinct advantages: 1) *Comparability*—measures have been standardized to be patient-centered, rather than disease-specific, permitting comparisons of patient outcomes between the Navigator and Usual care groups despite enrolling patients with multiple conditions; 2) *Reliability* and *Validity*—metrics for each domain have been rigorously reviewed and tested; 3) *Flexibility*—PROMIS measures can be administered in a variety of ways (in person, telephone, or via computer adaptive testing); for PArTNER, the baseline visit occurred while the patient was in the hospital, so administration was in person. Follow-up visits were performed by telephone to minimize participant burden (a key principle in effectiveness trials); and 4) *Inclusiveness*—PROMIS encompasses all people, regardless of literacy, language, physical function, or life course.

#### Secondary outcomes

2.10.2

Secondary outcomes include assessments of change in participant PROMIS anxiety and in informational support T-scores from enrollment to 60 days after hospital discharge, as well as changes of other PROMIS measures (instrumental support [version 2.0, SF4a, 4 items; emotional support [version 2.0 SF4a, 4 items], mental health [version 1.1 SF, 4 items within the 10-item global health scale], physical health [version 1.1 SF, 4 items within the 10-item global health scale]) from enrollment to 30 and 60 days after [27].

We will also assess healthcare utilization as secondary outcomes. We will assess attendance at outpatient clinics within 14 days of hospital discharge (using self-report; and separately using review of electronic health records at UI Health, which is shared with the hospital and all ambulatory clinics within health system, including a network of 11 federally qualified healthcare centers); death at 30 and 60 days after hospital discharge (based on caregiver report or review of electronic health records); rehospitalization at 30 and 60 days (assessed by review of electronic health records); emergency department visit at 30 and 60 days (assessed by review of electronic health records); death or re-hospitalization at 30 and 60 days; and finally, death or re-hospitalization or emergency department visit at 30 and 60 days. We do not have access to claims data to ascertain healthcare outside of the hospital or ambulatory clinics outside UI Health.

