B. Offer and assist with participant-specific needs by helping patients to identify and receive assistance from resources	• Development of a tailored, patient-centered plan for solutions to each identified barrier. Resources included those available through Purple Binder (website that houses information for medical and social service resources in the Chicago area) and those used by the hospital's social work department. • Review of solutions with the participant during subsequent visits and/or through email and text messages. • Reassessment of barriers and identification of new ones during each CHW in-hospital encounter. • Caregivers included in the discussions if requested by participant.
C. Completion of a “Discharge Patient Education Tool”	• Completion of personalized discharge patient educational tool (DPET) based on discharge instructions in the electronic health records. • Core content areas reviewed with participant using teach-back: - Post-discharge follow up visits and tests, - Recommendations regarding lifestyle changes, and - Use of medications after discharge. • CHW scheduled post-discharge follow-up appointments as needed. • Review of previously-identified barriers and potential solutions, including post-discharge resources and services. • Scheduling of home visit of CHW within 3 business days of hospital discharge. • Referral to the participant's clinicians for medical advice. - The CHWs were specifically instructed to not provide medical advice.
D. Re-review the DPET with the participant	• During home visit, review of DPET with the participant, including: - Reminder of upcoming tests and appointments - Confirmation of availability of transportation to tests and appointments - Review understanding and adherence to lifestyle changes - Confirmation of availability of medications - Confirmation of understanding and adherence to medications • If the participant had difficulty adhering to the DPET, peer coached identified new barriers and worked with participant to find a solution. • Participants encouraged to contact the hospital's social worker or clinician's office, if needed.
E. Re-review solutions to barriers with patient	• Review solutions implemented for previously identified barriers. • If needed, identification of new barriers and potential solutions

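### Rehospitalisation and emergency department visits are taken from UI Health records alone, although the masked 30- and 60-day calls could help recover outside events and allow a check on capture by arm

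*Protocol article*

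**What the plan says.** Section 2.10.2 names a source for each utilisation outcome:

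- Rehospitalisation: "rehospitalization at 30 and 60 days (assessed by review of electronic health records".
- ED visits: "emergency department visit at 30 and 60 days (assessed by review of electronic health records".
- Clinic attendance within 14 days, from two sources: "using self-report; and separately using review of electronic health records at UI Health".
- Death, from either of two sources: "based on caregiver report or review of electronic health records".

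The same section ends with the authors' own statement of the gap: "We do not have access to claims data to ascertain healthcare outside of the hospital or ambulatory clinics outside UI Health".

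Section 2.8 provides telephone follow-up by a coordinator masked to allocation: "Up to 14 call attempts will be made to collect patient-reported outcomes for each of the 30- and 60-day assessments". It adds that electronic records will be reviewed at both time points, chiefly for utilisation.

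Section 2.4 says that 95% power on the co-primary outcomes was chosen so that the sample would also give 80% power for a fall in 30-day death or rehospitalisation from 30% to 22.5%. Section 2.11 tests all outcomes other than the co-primaries at a two-sided 0.05.

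**The concern.** The two outcomes most exposed to care elsewhere are the two that rest on a single institution's record. The neighbouring outcomes in the same paragraph have a second, report-based source. The contacts needed to ask about outside stays and ED visits are already planned, masked, and timed to the outcome windows.

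Two things are at stake. First, if outside events are missed equally in both arms, the absolute difference shrinks and power falls for an outcome that influenced the sample size and that section 2.7 presents as of interest to payers and administrators. Second, if the share missed differs by arm, the comparison is biased. Masked record review does not protect against this, because the problem lies in which events enter the record and not in how they are read.

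**Working it through.** **Inputs from the protocol article.** n = 565 per arm, p1 = 0.30 and p2 = 0.225 for 30-day death or rehospitalisation, and 20% attrition (section 2.4). Two-sided alpha is 0.05 for secondary outcomes (section 2.11).

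**Input assumed.** The share f of composite events that the record captures. The documents give no figure, so I use 70% to 100%.

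**Formula.** With d = p1 − p2 and p̄ = (p1 + p2)/2,

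power = Φ[(d − 1.96·SE0)/SE1], where SE0 = √(2p̄(1 − p̄)/n) and SE1 = √((p1(1 − p1) + p2(1 − p2))/n).

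**Step 1: the plan's own figure.** p̄ = 0.2625, SE0 = 0.02618, SE1 = 0.02608. Power = Φ[(0.075 − 0.05131)/0.02608] = Φ(0.908) = 0.818. The stated 80% reproduces if all 565 per arm are analysed. With 452 per arm (565 × 0.80) it is 0.727.

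**Step 2: equal capture in both arms.** Observed rates are f × 0.30 and f × 0.225. This scales the whole composite, which is a simplification.

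| Capture f (assumed) | Observed rates | Difference | Power, 565/arm | Power, 452/arm | n/arm for 80% |
|---|---|---|---|---|---|
| 100% | 30.0% vs 22.5% | 7.5 points | 0.818 | 0.727 | 540 |
| 90% | 27.0% vs 20.25% | 6.75 points | 0.762 | 0.667 | 621 |
| 80% | 24.0% vs 18.0% | 6.0 points | 0.698 | 0.601 | 723 |
| 70% | 21.0% vs 15.75% | 5.25 points | 0.625 | 0.531 | 854 |

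The risk ratio stays at 0.75 in every row. What shrinks is the absolute difference and the power.

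**Step 3: unequal capture (assumed, shown both ways).** True rates are 30% vs 22.5%.

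- Usual care 80%, Navigator 90%: 0.30 × 0.80 = 24.0% vs 0.225 × 0.90 = 20.25%. The difference is 3.75 points, with power 0.329 at 565 per arm.
- Usual care 90%, Navigator 80%: 27.0% vs 18.0%. The difference is inflated to 9.0 points.
- No true effect (30% in both arms), 80% vs 90%: 24.0% vs 27.0%, a false 3-point difference. With p̄ = 0.255, SE0 = 0.02593 and SE1 = 0.02592, the two-sided rejection rate is about 0.21 instead of 0.05.

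Step 3 shows only that modest imbalance matters and that its sign decides whether the effect is hidden or exaggerated. It is not evidence of which sign applies.

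**The case against.** The strongest reply is that the gap is disclosed, affects only secondary outcomes, and follows from a deliberate choice to limit participant burden (section 3). Sections 2.8 and 2.10.2 agree in naming the record for utilisation, so there is no contradiction. All of that stands. Disclosure does not, however, explain why calls that are already being made are left unused for these two outcomes.

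Three stronger readings are tempting, and the documents do not support them.

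- **That capture is higher in the Navigator arm, so the bias runs against Navigator.** A reader might infer this from Table 2, where "CHW scheduled post-discharge follow-up appointments as needed" and participants are pointed to the hospital's social worker if needed. But those appointments are outpatient visits with no site named, the participant's clinicians need not be at UI Health, and the community resources and peer coaches lie outside it. No passage says where participants would go when acutely ill.
- **That every outside admission is scored as no event.** The article does not say how an outside stay noted in the UI Health chart is handled. Incompletely captured is the most that can be said.
- **That failing to give the source of the 30% planning rate is itself a defect.** A condensed article commonly leaves that to the full protocol. It matters here only as a condition: if 30% is already a UI Health-only rate, the equal-capture loss in step 2 disappears.

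Two technical objections also stand. Deaths have a second source and should not be scaled like rehospitalisations. If the effect is proportional on both parts, the capture share of the composite is therefore higher than that of rehospitalisation alone. And self-report reaches only those who answer: section 2.4 assumes 20% attrition, section 3 warns of unstable housing and telephone contact, and Navigator participants receive up to five coaching calls, so response and reporting could themselves differ by arm. That is why self-report belongs in a supplementary analysis only.

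**Conclusion.** The point holds as an avoidable weakness in the ascertainment of secondary outcomes. The record-only source leaves outside rehospitalisations and ED visits incompletely captured, and as planned there is no second source with which to check capture by arm.

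On size, the equal-capture loss is from 0.818 to 0.762, 0.698 or 0.625 at assumed shares of 90%, 80% or 70%. It rests on three conditions: the 30% is an all-hospital rate, all 565 per arm are analysed, and the share applies to the whole composite. Differential capture is possible, but its direction and size are unknown. The co-primary PROMIS outcomes and their analysis are unaffected.

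**What to change.** - Add two items to the existing masked 30- and 60-day calls: any overnight hospital stay, and any ED visit, at any hospital.
- Keep the record-only definition as the main analysis, since it does not depend on reaching the participant by telephone.
- Pre-specify a record-or-self-report definition of rehospitalisation, ED visit and both composites as a sensitivity analysis.
- Report, by arm, the share of events known only from self-report and the call response at each time point, so that the sensitivity result can be read against any imbalance in response.

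The cost is two more interview items and one parallel analysis. The downsides are recall error, and non-response or reporting that may itself differ by arm.
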